### Combining cognitive interventions with evidence-based treatments to promote full recovery

An overarching aim of our research is to develop treatment packages which promote functional and symptomatic recovery for individuals with mood disorders. The current trial incorporates medication management, psychological therapy, and targeted CR approaches in order to achieve this. Research indicates that CR interventions which integrate principles of psychological therapy (e.g., role-play, goal setting) alongside a therapeutic relationship produce better retention rates, and improved self-reported cognitive and functional competence compared with traditional CR approaches [24]. We selected Interpersonal and Social Rhythm Therapy (IPSRT) as our long-term therapy to provide alongside CR. IPSRT is a psychological therapy developed for BD which focuses on stabilising circadian and social rhythms (e.g., sleep), as well as improving interpersonal functioning. Data suggests a link between disrupted sleep and cognitive [25] and functional impairment [26] in BD. Thus, improving sleep patterns alongside a CR intervention has a solid theoretical basis. Furthermore, IPSRT has been shown to be effective in reducing depression symptoms and reducing risk of relapse in BD [27, 28] and similar preliminary effects have been reported in MDD [29]. A treatment package including IPSRT and CR, therefore, has potential to improve several key aspects of recovery from mood disorders.

### Development of the current trial

We have recently completed a pragmatic RCT [30] which examined a novel combination of CR, IPSRT and medication management for people with mood disorders. Individuals (*n* = 68) recently discharged from SMHS in Christchurch, New Zealand, were recruited into the trial and randomised to receive a 12-month course of IPSRT either with (IPSRT-CR) or without CR (IPSRT alone). For those randomised to IPSRT-CR, CR was incorporated into the 50-min therapy sessions from an early stage of treatment and continued for 12 sessions. However, the addition of CR to IPSRT did not significantly improve the primary outcome, Global Cognition, more than IPSRT alone. On the other hand, significantly greater improvement in psychosocial functioning and longitudinal depression symptoms was evident in the IPSRT group compared with the IPSRT-CR over the treatment period. During the trial, therapists had concerns about integrating CR into IPSRT at such an early stage of treatment. At study intake, 43% of the sample were ‘in episode’, and thus, therapists often prioritised stabilisation of mood over CR. This was a factor contributing to the comparatively low dose of CR (average of 7 h) provided in our trial compared with other recent RCTs of CR in BD [21, 22]. We therefore propose a follow-on RCT which will once again aim to optimise psychological treatment to improve cognitive function, and thereby, to improve functioning and mood outcomes in individuals with mood disorders. However, the CR component will, in this trial, be conducted at a later stage of treatment and will be delivered separately from ongoing IPSRT. For the first 6 months of the 12-month intervention period, all individuals will receive the same intervention; individual IPSRT. At 6 months, individuals will be randomised to receive additional group-based CR (8 sessions over 8 weeks) or no additional treatment. Shifting to a group approach should allow for a higher and more consistent dose of CR to be delivered, and at a point when individuals should have a more stable mood.

An issue for psychological treatment trials is often translatability into clinical practice [31]. Conducting trials in patients with very thoroughly defined characteristics has advantages for determining effectiveness of treatments and understanding their mechanisms but has disadvantages in translation since in clinical practice it is necessary and more feasible to deliver treatments to broader groups of patients. As with our previous RCT described above, the current trial will thus recruit individuals across the spectrum of mood disorders (BD and MDD) at a particular point in their contact with services; that is, on discharge from SMHS.

### Factors associated with cognitive impairment and response to cognitive interventions

Factors influencing response to CR are important to identify in order to be able to determine how to tailor interventions to individuals’ cognitive and clinical profiles. This, in turn, should maximise treatment engagement and success. One of the more consistent predictors of CR response is baseline cognitive performance, with poorer performance associated with greater improvement from CR interventions [32]. Less is known about the impact of subjective cognitive difficulties on CR treatment response, but the finding that subjective cognitive difficulties relate to relapse in a large MDD sample receiving antidepressant treatments [33] indicates the importance of investigating this factor further in this context. Several measures of subjective cognitive difficulties, as well as factors likely to be associated with subjective cognitive difficulties (rumination, metacognition, mood severity) are included in the current protocol to determine their impact on CR response in secondary and exploratory analyses. Other factors to be included in exploratory analyses include: childhood trauma, personality traits, circadian rhythm disturbance, and medication adherence (see Methods).

Measurement of key biological processes implicated in mood disorder aetiology and cognitive impairment will occur in this trial, including assessing levels of inflammatory markers (pro-inflammatory cytokines and C-Reactive Protein; CRP) [34–36], vitamin C [37, 38], and androgens (females only) [39]. To be able to comprehensively treat cognitive impairment, the underpinnings of cognitive impairment must be more fully understood; obtaining these biological data will help inform this understanding.

### The patient perspective

One important perspective that has been overlooked in most clinical trials of CR to date is the patient perspective of cognitive impairment, and of undergoing cognitive interventions. Cognitive and functional symptoms of mood disorders have been described by patients as some of the most debilitating and concerning aspects of the disorders [40], and qualitative research has highlighted the broad impact cognitive impairment has on peoples’ lives and sense of self [41]. More in-depth understanding of patient perspectives will be examined in a qualitative study embedded within this trial.

## Methods and design

See Fig. 1 for study flow and Table 1 for key time-points for interventions and assessments.

**Fig. 1 Fig1:**
[figure not shown]
CONSORT flow diagram. The flow chart depicts participant progression through the study from initial enrolment through allocation, follow-up and analyses

**Table 1 Tab1:**
[figure not shown]
Schedule of enrolments, interventions, and assessments

### Aim

To compare the effectiveness of a 12-month intervention involving IPSRT combined with group-based CR (IPSRT-CR), with IPSRT alone, on cognitive functioning (primary outcome, Global Cognition), general functioning, and mood symptoms in individuals with mood disorders, at the point of discharge from SMHS in Christchurch.

### Primary hypothesis

Individuals randomised to receive IPSRT-CR will show significantly improved Global Cognition between 6-month (prior to commencing CR) and 12-month (treatment-end) time-points compared with individuals randomised to receive IPSRT alone.

Secondary hypotheses.Significant improvement in longer-term Global Cognition (18 months) will be found in IPSRT-CR versus IPSRT alone groups.General and psychosocial functioning will improve significantly more in IPSRT-CR versus IPSRT groups at treatment-end and follow-up time-points (18 and 24 months).Measures of mood symptoms (longitudinal depression symptoms, mood disturbance) will improve significantly more in the IPSRT-CR versus IPSRT alone groups at treatment-end and follow-up time-points.

### Trial design

See Fig. 1 for the study flow chart. This is a prospectively-registered (Australian and New Zealand Clinical Trials Registry; ref ACTRN12619001080112; 6 August 2019), two-arm, single-blinded RCT comparing IPSRT-CR with IPSRT alone for individuals with mood disorders. The trial was approved by the New Zealand Health and Disability Ethics Committees (Northern B) on 16 May 2019 (19/NTB/54). All participants will provide written informed consent. This RCT will be conducted and reported in accordance with SPIRIT (Standard Protocol Items; recommendation for Interventional Trials) [42] and CONSORT (Consolidated Standards of Reporting Trials) [43] guidelines. Recommendations specifically related to the design of CR trials from the International Society of Bipolar Disorder (ISBD) Targeting Cognition Taskforce have also guided development of this trial methodology [5].

### Setting

The study will take place in the Clinical Research Unit at the Department of Psychological Medicine, University of Otago, Christchurch, in collaboration with the Canterbury District Health Board.

### Participants

One hundred adults (≥ 18 years old) with MDD or BD (I, II, or Not Otherwise Specified) will be referred by treating clinicians at SMHS to the trial at the point at which individuals would typically have been discharged back to primary care. Diagnosis will be confirmed with the Structured Clinical Interview for DSM-5 Disorders, Research Version (SCID-5-RV) [44]. Patients must be identified by their referring clinician as showing evidence of cognitive impairment or identify this themselves. The screening question will be: “are you [or is the patient] having any difficulties with concentration, memory or decision-making?” (see Discussion for rationale). Exclusion criteria will include: schizophrenia or schizoaffective disorder, severe alcohol or drug dependence, history of severe brain injury (loss of consciousness greater than 1 h), previous course of CR or electroconvulsive therapy in past 12 months, serious medical or neurological condition affecting cognitive function, and pregnancy.

### Randomisation

Randomisation to the group-based CR intervention, or not, will occur at 6 months. This time-point has been chosen to avoid differential early dropout based on randomisation and to provide a period of mood stabilising treatment prior to CR treatment. Computerised permuted block randomisation will be undertaken by the team’s biostatistician (CF) prior to the commencement of the study and will be stratified according to mood disorder type (BD or MDD). Sequentially numbered envelopes will be stored in a locked cabinet by an independent research coordinator and given to therapists after the 6-month research assessment. Each patient will be allocated a randomisation number which will not be re-allocated if the patient drops out of the study.

### Interventions

#### Interpersonal and Social Rhythm Therapy

IPSRT combines Interpersonal Psychotherapy with a focus on social rhythms or routines in a person’s life. IPSRT will be delivered in an individual format by 8 clinicians (2 clinical psychologists, 5 mental health nurses, 1 social worker) trained in the provision of IPSRT, according to a manualised protocol. This has been adapted from the original IPSRT manual [45] by experienced IPSRT therapists (MI, MC) for patients with MDD as well as BD [29].

IPSRT will be conducted over a period of 12 months (weekly for the first 10–12 weeks, fortnightly for four months, and then monthly). Therapy frequency may increase, however, according to the patient’s mental state. A total of 24 sessions will be considered a full therapy dose, and 18 sessions as treatment completion.

#### Group-based cognitive remediation

CR involves engaging in cognitively stimulating activities that can produce changes in brain function [46]. We have previously employed an individual format for CR in our trials [30, 47], however, in order to increase patient engagement, to improve generalisability to ‘real-world’ functioning, and to allow for both IPSRT and CR components of therapy to be provided in a more structured and comprehensive manner, we have moved to a group-based CR format. Group-based CR is a well-established format in schizophrenia and mood disorders [48].

Group-based CR will involve weekly 90-min sessions over 8 weeks (i.e., 8 sessions). The group-CR manual used in the current study has been adapted for New Zealand from the original Action-based Cognitive Remediation (ABCR) manual developed by [name] (Queen’s University, Canada); we have termed it ABCR-NZ. Adaptations involved changes in language to reflect New Zealand English or te reo Māori, and changes to some of the ‘real-life’ tasks (described below) to reflect situations more realistic in New Zealand. We modified the frequency (once weekly) and duration (90 min) of CR sessions from the ABCR programme described in Bowie et al. [24]. We also reduced the number of modules covered (3 modules from ‘Speed and Attention’, 2 modules from ‘Learning and Memory’, 2 modules from ‘Executive Functioning’ and 1 module from ‘Social Cognition’; 1 module per session). These changes were made to reduce participant time burden, in the knowledge that many participants would be in full-time employment and many would still be attending fortnightly IPSRT sessions.

Each ABCR-NZ session involves four main components, described in detail in Bowie et al. [24]:*Computerised cognitive training*: Computerised cognitive training techniques are used with an online program called Scientific Brain Training Pro (SBT-Pro; www.scientificbraintrainingpro.com). SBT-Pro exercises use drill and practice procedures for training cognitive abilities including attention, processing speed, visual memory, verbal memory, working memory, and executive functions. Each exercise has several levels of difficulty that automatically adjust according to patients’ performance. They are game-like in nature and provide immediate feedback. A fixed schedule of exercises will be used wherein one exercise is practiced each group-CR session. For each module, a further two exercises relating to the module theme (e.g., learning and memory) can be practiced outside of sessions. During group-CR sessions, participants will complete exercises independently on a study tablet for approximately 20 min, with a therapist present to assist if required. In addition to the in-session computer exercises, participants are encouraged to practice these exercises for 30 min each day between group sessions, with therapists able to provide online feedback.*Strategy monitoring*: when participants are practicing computerised exercises, therapists will encourage them to think about strategies they are using. Following this, patients share these strategies with group members and therapists may facilitate this discussion and document strategies on a whiteboard.*Simulated real-life role-plays and tasks*: this involves engagement in simulated ‘real-world’ tasks and role-plays, as described in Bowie et al. [24]. These tasks are in line with the theme of each session. For example, in a group-CR session from the ‘Learning and Memory’ module, a real-life task involves a hypothetical work orientation day in which every group member introduces themselves (using a blurb provided by the therapist) and is then required to use cognitive strategies to recall information about other group members and then to introduce them to the group. Transfer strategies used in ABCR-NZ are tangible, procedural, and realistic.*Transfer discussion and cognitive activation*: the final component of each ABCR-NZ session involves group discussion about how computerised exercises and real-world simulations relate to activities in everyday life, followed by identification of cognitively-stimulating activities to work on between sessions.

CR treatment will occur in the final 6 months of each patient’s treatment, and will be commenced between approximately months 6 to 9 depending on patient numbers (see Discussion for rationale).

There will be 3 to 5 patients in each group, and two therapists. The trial lead, KD (Clinical Psychologist), received in-person training in ABCR in June 2019 from [name] and his lab members, and KD has trained all ABCR-NZ group therapists (4 mental health nurses, 1 psychiatrist) for the current protocol.

With regards to fidelity of both IPSRT and group-CR interventions, therapy sessions will be audio-taped and 10% randomly selected and rated to ensure adherence to IPSRT and CR therapy protocols using checklists for key components of each therapy (as in Douglas et al. [30]). Therapists participate in fortnightly group supervision, led by therapists with extensive experience in training and delivery of IPSRT (MI) and CR (KD).

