#### Power

This study is powered on the cognitive outcomes demonstrated in our preliminary RCT of Metacognitive Therapy versus Cognitive Behavioural Therapy for outpatients with MDD [16]. Metacognitive Therapy includes a simple cognitive training intervention (Attention Training Technique). A positive effect size difference between Metacognitive Therapy and Cognitive Behavioural Therapy was found on measures of visuospatial learning and attention (0.6) [16]. To detect a similar effect size for Global Cognition as statistically significant (2-tailed α = 0.05), 45 patients per group would be necessary for 80% power. We aim to recruit 50 patients per group. All statistical tests will utilise a 2-tailed *p*-value of < 0.05 to indicate statistical significance.

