#### Analysis of primary outcome

Global Cognition will be calculated by averaging *Z*-scores across each cognitive domain, as listed above. A change *z*-score from 6- to 12-month follow-up will then be calculated using the Global Cognition score from these time-points. Change *z*-scores on Global Cognition will be compared using general linear models, with an intention-to-treat (ITT) approach. Treatment arm (IPSRT-CR versus IPSRT) and stratum (MDD versus BD) will be fixed factors, as in Douglas et al. [30].

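### CR is given in small groups in one arm only, but the stated model and sample size treat all participants as independent; if outcomes correlate within CR groups, the 5% test is modestly anti-conservative

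*Protocol article*

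**What the plan says.** **Delivery.** The section on group-based cognitive remediation states: "There will be 3 to 5 patients in each group, and two therapists". The other arm has no counterpart. Under Development of the current trial, at 6 months "individuals will be randomised to receive additional group-based CR (8 sessions over 8 weeks) or no additional treatment". Interaction is part of the treatment: during sessions "patients share these strategies with group members and therapists may facilitate this discussion", and there are role-plays and a closing group discussion. The start of CR, between about months 6 and 9, depends on patient numbers, so members of one group also share an approximate start date.

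**Analysis.** For change in Global Cognition from 6 to 12 months, Analysis of primary outcome specifies general linear models by intention to treat: "Treatment arm (IPSRT-CR versus IPSRT) and stratum (MDD versus BD) will be fixed factors". Analysis of secondary and exploratory outcomes repeats the same two factors. Neither section has a term for CR group or group therapist.

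**Sample size.** With a standardised effect of 0.6 and two-sided alpha 0.05, the Power section says "45 patients per group would be necessary for 80% power", and then "We aim to recruit 50 patients per group". It names neither an ICC nor a design effect, and gives no reason for going from 45 to 50.

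**The concern.** This is a partially nested design: participants in one arm are clustered in treatment groups, and those in the other are not. Members of a CR group share therapists, discussion, joint tasks and roughly the same interval between finishing CR and the 12-month assessment. Timing of research assessments itself says that effects are best detected directly after CR, so that shared interval is a plausible source of correlation in the primary outcome.

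A general linear model with arm and stratum assumes independent errors. If outcomes correlate positively within CR groups, the mean of the IPSRT-CR arm varies more than the model reckons. The confidence interval is then too narrow and the p-value too small, for the primary outcome and for every outcome analysed in the same way. False-positive claims of benefit from CR become somewhat more likely. A test that keeps its 5% level would have less power than the independent-observations figure.

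A protocol article may leave much to an analysis plan, but this one names the model and its terms, so the point concerns a stated choice.

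**Working it through.** **Inputs from the protocol.** Effect 0.6, two-sided alpha 0.05, 80% power at 45 per group and target 50 per group (Power); CR group size m of 3 to 5 (Group-based cognitive remediation). With 50 allocated to CR this gives 50/5 = 10 to 50/3 ≈ 17 groups.

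**Assumed.** The ICC of the 6-to-12-month change within CR groups (range 0.02 to 0.15), and equal total variance in the two arms.

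**Step 1: reproduce the stated figure.** A two-sample t-test with independent observations has power 79.5% at 44 per group, 80.4% at 45 and 84.4% at 50. The stated 45 is therefore the independent-observations figure, with no allowance for clustering.

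**Step 2: variance of the treatment difference.**
- Design effect in the CR arm: DE = 1 + (m − 1) × ICC.
- True variance divided by the model's variance: R = (DE + 1)/2, since only one arm is inflated.
- The true standard error is √R times the model's.

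Example, m = 4 and ICC 0.10: DE = 1 + 3 × 0.10 = 1.30, R = 2.30/2 = 1.15, √R = 1.072.

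**Step 3: type I error of the planned model.** 2 × [1 − Φ(1.96/√R)]. In the example 1.96/1.072 = 1.828, which gives 6.8%.

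**Step 4: power of a test that holds its 5% level.** Two-sample t-test with effect 0.6/√R. In the example 0.6/1.072 = 0.560, which gives 74.7% at 45 per group and 79.1% at 50.

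| m | ICC | DE | True SE ÷ model SE | Type I error | Power, 45 per group | Power, 50 per group |
|---|---|---|---|---|---|---|
| any | 0 | 1.00 | 1.000 | 5.0% | 80.4% | 84.4% |
| 4 | 0.02 | 1.06 | 1.015 | 5.35% | 79.2% | 83.3% |
| 4 | 0.05 | 1.15 | 1.037 | 5.9% | 77.5% | 81.7% |
| 4 | 0.10 | 1.30 | 1.072 | 6.8% | 74.7% | 79.1% |
| 5 | 0.15 | 1.60 | 1.140 | 8.6% | 69.5% | 74.1% |

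**Step 5: checks.**
- *Simulation* of the unadjusted t-test (40,000 replicates, m = 4, 48 per arm) gave type I error 5.9% at ICC 0.05 and 6.7% at 0.10, in agreement with the formula.
- *Small-sample degrees of freedom.* With Satterthwaite degrees of freedom and m = 4, power at ICC 0.05 and 0.10 is 75.7% and 72.7% at 45 per group, and 80.3% and 77.4% at 50.
- *Non-attendance.* If 80% of those allocated to CR attend a group (an assumption), with m = 4 and ICC 0.10, the design effect averaged over the arm is 1 + 0.8 × 0.30 = 1.24, R = 1.12, and type I error is 6.4% instead of 6.8%.

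**The case against.** **The ICC may be close to zero.** The protocol gives reasons to expect this. The computer exercises are done alone on a tablet and adapt to each patient, and practice is encouraged between sessions. Delivery is manualised, one person trained all the group therapists, and a sample of sessions is rated for adherence. The primary outcome is individual objective testing by a blinded assessor, often some time after the group has ended. A reader might infer that the standard error is certainly too small. The documents do not support that: at ICC 0 there is no error, and at 0.02 it is negligible. This stands, and it makes the finding conditional.

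**The target is 50 per group, not 45.** A reader might infer that the trial is underpowered. At 50 analysed per group, power stays at or above 80% up to an ICC of about 0.12 (m = 3), 0.083 (m = 4) or 0.062 (m = 5). This stands in large part. Three limits apply: the protocol does not assign the extra patients to clustering, recruitment precedes the 6-month randomisation so that 50 randomised per arm is not assured, and small-sample degrees of freedom lower these thresholds.

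**Unequal variances.** A reader might also infer that the arms must differ in variance. Nothing in the protocol shows this, and the calculation above assumes equal total variance.

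**Detail for the analysis plan.** The degrees-of-freedom method and the recording of a group identifier normally sit outside an article, and attendance must be recorded anyway for the completers analysis. That is fair, but the model terms themselves are fixed here.

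**Conclusion.** The point holds in conditional form. CR is given in interacting groups in one arm only, while the stated models and the sample size treat all participants as independent. If outcomes correlate positively within CR groups, the nominal 5% test is modestly anti-conservative: 5.35% to 6.8% for groups of 4 and ICC 0.02 to 0.10, up to 8.6% for groups of 5 and ICC 0.15, and somewhat less if some allocated patients never attend.

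The type I error is the sturdier part, because recruiting 50 instead of 45 leaves it unchanged. The power part is weaker: the 80% tied to 45 per group falls to between 79.2% and 74.7% over ICC 0.02 to 0.10, but at 50 per group it is 83.3% to 79.1%. All sizes rest on an assumed ICC. The absence of any allowance is certain from the text; its magnitude is not.

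**What to change.** - In the primary, secondary and exploratory models, add a random intercept for CR group in the IPSRT-CR arm only. Treat control participants and CR participants who never attend as clusters of one, and use small-sample degrees of freedom (for example Kenward-Roger or Satterthwaite).
- Keep the CR group identifier in the analysis dataset.
- Restate power at 45 and 50 per group over a stated ICC range, and say whether the five extra patients per group are meant to cover clustering.

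**Cost.** Changed analysis wording and one retained variable; treatment and recruitment are unaffected. The interval becomes slightly wider and the stated power slightly lower. With about 10 to 17 groups the group variance will be imprecisely estimated and may come out as zero, so a near-zero estimate should not be read as proof that there is no clustering.
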